## Abstract

Creatine is an essential metabolite for brain function, with a fundamental role in cellular (ATP) energy homeostasis. It is hypothesized that preterm infants will become creatine deplete in the early postnatal period, due to premature delivery from a maternal source of creatine and a limited supply of creatine in newborn nutrition. This potential alteration to brain metabolism may contribute to, or compound, poor neurological outcomes in this high-risk population. Understanding Creatine for Neurological Health in Babies (UNICORN) is an observational study of circulating and cerebral creatine levels in preterm infants. We will recruit preterm infants at gestational ages 23^+0^–26^+6^, 27^+0^–29^+6^, 30^+0^–32^+6^, 33^+0^–36^+6^, and a term reference group at 39^+0^–40^+6^ weeks of gestation, with 20 infants in each gestational age group. At birth, a maternal capillary blood sample, as well as a venous cord blood sample, will be collected. For preterm infants, serial infant plasma (heel prick), urine, and nutrition samples [total parenteral nutrition (TPN), breast milk, or formula] will be collected between birth and term “due date.” Key fetomaternal information, including demographics, smoking status, and maternal diet, will also be collected. At term corrected postnatal age (CPA), each infant will undergo an MRI/^1^H-MRS scan to evaluate brain structure and measure cerebral creatine content. A general movements assessment (GMA) will also be conducted. At 3 months of CPA, infants will undergo a second GMA as well as further neurodevelopmental evaluation using the Developmental Assessment of Young Children – Second Edition (DAYC-2) assessment tool. The primary outcome measures for this study are cerebral creatine content at CPA and plasma and urine creatine and guanidinoacetate (creatine precursor) concentrations in the early postnatal period. We will also determine associations between (1) creatine levels at term CPA and neurodevelopmental outcomes (MRI, GMA, and DAY-C); (2) dietary creatine intake and circulating and cerebral creatine content; and (3) creatine levels and maternal characteristics. Novel approaches are needed to try and improve preterm-associated brain injury. Inclusion of creatine in preterm nutrition may better support *ex utero* brain development through improved cerebral cellular energy availability during a period of significant brain growth and development.

**Ethics Ref:** HDEC 18/CEN/7 New Zealand.

**ACTRN:** ACTRN12618000871246.

## Introduction

The global incidence of preterm birth (delivery prior to 37 completed weeks of gestation) is reported to be ~11% (Blencowe et al., 2013). Advances in perinatal care mean that increasing numbers of infants born even at extremes of gestational age (extreme preterm: <28 weeks of gestational age) survive beyond the neonatal period (Davidoff et al., 2006; Mohangoo et al., 2011; Lawn et al., 2013). Additionally, within resource-rich neonatal care settings, the age of human viability continues to fall with increasing survival rates at even 22 and 23 weeks of gestational age. However, this increase in survival has not been coupled with a reduction in long-term morbidity. Neurodevelopmental disorders, including those of executive function, psychiatric, and behavioral sequelae (Blencowe et al., 2013), are more prevalent in those born preterm than at term, with increasing risk, the lesser the gestational age at birth (Crump et al., 2010; Johnson et al., 2010).

The etiology of brain injury in preterm infants is complex and often unexplained. Historically, intraventricular hemorrhage (IVH) with resultant disruption of brain tissue and formation of macrocystic lesions was associated with global developmental delay. With the improvements in perinatal care, high grade IVH and/or periventricular leukomalacia (PVL) has become far less common, and standard cranial ultrasound or magnetic resonance imaging (MRI) examination usually do not demonstrate gross structural lesions (Penn et al., 2016). In Australia and New Zealand, the rate of high grade IVH in infants born prior to 32 weeks’ gestation declined from 8% to just over 4% in the period between 2004 and 2013 (Chow et al., 2013). As such, longitudinal studies now indicate that a large percentage of children born preterm have neurodevelopmental problems in the absence of structural brain abnormalities detected with conventional imaging (Constable et al., 2008; Mullen et al., 2011; Aeby et al., 2013). These data suggest that conventional prognostication based on measures of cerebral structure is poorly discriminatory and will not always identify infants at risk of neurodevelopmental morbidity. We, and others, propose that our focus should be widened to explore the role of altered brain metabolism in the pathophysiology of preterm brain injury and neurodevelopmental disability (Koob et al., 2016).

Creatine is a metabolite essential for brain development and energy metabolism (Braissant et al., 2007). It is an amino acid derivative that fuels the creatine kinase circuit; a phosphagen system that mitigates temporal imbalances in energy (ATP) supply and demand (Wallimann et al., 1992). *Via* the creatine kinase circuit, creatine and its phosphorylated derivative (phosphocreatine, PCr) shuttle high-energy phosphate groups from the mitochondria into the cytosol, for the regeneration of ATP from ADP (Ellington, 2001). The creatine kinase isoforms required to run the circuit are found in the cerebellum, choroid plexus, hippocampal granular layer, and pyramidal cells of the brain (Hemmer et al., 1994) and are involved in maintaining ATP homeostasis in the central nervous system (CNS) from early in embryonic development through to adulthood (Braissant et al., 2001; Braissant et al., 2007).

Both creatine and phosphocreatine are spontaneously broken down into creatinine at a rate of ~1.7%/day (Brosnan and Brosnan, 2007). Thus, there is a requirement to replenish creatine and PCr stores on a daily basis. Creatine can be obtained from the diet and is also endogenously synthesized *de novo*. Synthesis involves the production of guanidinoacetate (GAA) from arginine and glycine, in a reaction catalyzed by arginine:glycine aminotransferase (AGAT) that occurs predominately in the kidney and pancreas. GAA is then methylated by guanidinoacetate N-methyltransferase (GAMT), mainly in the liver, to produce creatine. Once synthesized or absorbed, creatine is transported into cells *via* the sodium-dependent SLC6A8 creatine transporter (Wyss and Kaddurah-Daouk, 2000). Creatine is able to cross the blood-brain barrier (Ohtsuki et al., 2002), and the brain itself also has some inherent capacity to synthesize creatine, with both AGAT and GAMT expressed by neurons, astrocytes, and oligodendrocytes (Braissant et al., 2001; Tachikawa et al., 2004; Nakashima et al., 2005). Despite the importance of creatine for brain growth and development, the relative importance of cerebral creatine derived from systemic rather than local synthesis has not yet been established.

*In utero* fetal magnetic resonance spectroscopy (^1^H-MRS) studies indicate cerebral creatine accretion occurs from 18 to 40 weeks of gestation (Evangelou et al., 2015). Postnatal studies have also clearly identified that an increase in cerebral creatine concentration occurs during the first 3 months of life (Blüml et al., 2012; Blüml et al., 2014). The importance of a maternal source of creatine for the developing fetus and the continued postnatal accretion of cerebral creatine is made evident by those infants diagnosed with inherited creatine deficiency syndromes. These infants typically raise no concerns antenatally; however, as postnatal creatine levels fall, they become progressively more symptomatic with altered neurological state (Almeida et al., 2006) and complex neurological symptoms including impaired psychomotor development, seizures, and cognitive impairment (Battini et al., 2006).

In adults, creatine is acquired *via* the diet and *de novo* synthesis, with each contributing ~50% (Brosnan and Brosnan, 2007). However, in infancy, due to low levels of creatine in human breast milk and commercial formulas, a term infant most likely synthesizes between 64 and 93% of their daily creatine requirements (Edison et al., 2013). The age at which a fetus/newborn develops the capacity to synthesize creatine is currently unknown, but it requires sufficient renal, hepatic, and cerebral maturity to express the enzymes necessary for creatine synthesis. Evaluation of AGAT and GAMT expression in the rat embryo found that AGAT was expressed in isolated cells of the CNS from 0.6 gestation; however, widespread expression of AGAT and rudimentary GAMT expression were not apparent before 0.8 gestation (Braissant et al., 2005). Our own studies in the precocial spiny mouse found that the fetal kidney and liver do not express AGAT and GAMT before 0.9 gestation, an age and maturation equivalent to ~35 weeks’ human gestation (Ireland et al., 2009). Taken together, these observations raise compelling questions about progressive creatine depletion in preterm infants, and whether this complication of nutritional compromise predisposes or compounds their risk of altered cerebral metabolism and thus long-term neurodevelopmental disability.

To date, a number of small observational studies have identified perturbations in creatine homeostasis in preterm infants (Blüml et al., 2014; Koob et al., 2016). Koob et al. (2016) reported that at term CPA creatine concentrations in the centrum semiovale of infants born preterm (born 29.1 ± 2 weeks) were reduced compared to those born at term (Koob et al., 2016). In addition, Lage et al. (2013) found that by hospital discharge, preterm infants had higher urinary GAA and reduced urinary creatine excretion, suggesting differences in systemic creatine synthesizing capacity. This was particularly apparent in their very preterm group (28–29 weeks) (Lage et al., 2013).

No studies have characterized longitudinal changes in creatine metabolism among preterm infants or the association between cerebral creatine content and neurodevelopmental outcomes. Further to this, no studies have monitored systemic creatine levels (both circulating and excreted) in a single preterm population nor have they assessed nutritional creatine availability for preterm infants fed with total parenteral nutrition (TPN), preterm infant formulas, or breast milk.

We hypothesize that following preterm birth, peripheral and cerebral creatine levels will fall, so that at term CPA, preterm infants will have relative systemic and cerebral creatine deficiency. Furthermore, this reduction in creatine bioavailability will jeopardize normal brain metabolism and development, ultimately predisposing the infant to neurodevelopmental dysfunction.

The overall aim of this study is to assess whether preterm infants become creatine deplete in the early postnatal period, by measuring the preterm infants’ circulating and excreted levels of creatine and GAA and comparing these measures to cerebral creatine content, as determined by ^1^H-MRS, at term corrected age. This study will correlate preterm creatine levels with neurological outcomes using MRI, general movements assessment (GMA), and the Developmental Assessment of Young Children – Second Edition (DAYC-2) Test (Novak et al., 2017). This study will also establish the levels of creatine provided through dietary intake during the days and weeks after preterm birth. Results of this study may support the use of creatine supplementation as standard nutritional care of the preterm infant, in order to improve neurodevelopmental function in this vulnerable population.

### Specific Aims

Compare cerebral, plasma, and urine creatine and GAA content between preterm and term infants at CPA.Describe preterm infant plasma and urine creatine and GAA concentrations and creatine:GAA ratio in the early postnatal period.Describe associations between cerebral creatine content, plasma, and urine creatine concentrations with maternal and infant characteristics at CPA.Compare creatine, GAA, arginine, glycine, and methionine concentrations in standard preterm nutrition, including TPN, preterm infant formulas, and breast milk.Determine whether dietary source of creatine (TPN, formula, or breast milk) is related to plasma or urine creatine concentrations in the early postnatal period.Describe associations between cerebral creatine content and blood and urine creatine concentrations with neurological outcomes (GMA, MRI, and DAYC-2) at CPA and at 3 months of corrected postnatal age.

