### Primary Outcome Measures

Cerebral creatine content at term CPAPlasma (bi-weekly) and urine (weekly) creatine and GAA levels from birth until hospital discharge and at CPACreatine, GAA, and amino acid levels in infant nutrition (TPN, formula, or breast milk) supplied from birth until discharge and at CPA

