### Statistical Analysis

Characteristics of the population will be tabulated, along with appropriate descriptive statistics of the study sample. Continuous data will be assessed for normality and expressed as means and standard deviations or median and interquartile range as appropriate. Categorical data will be expressed as counts and proportions. Average creatine content from nutrition per week for each baby in the early postnatal period will be calculated.

Differences in creatine and GAA measures (^1^H-MRS, plasma or urine) between infants born preterm and those born at term will be assessed at CPA using a t-test or Mann-Whitney U test as appropriate. The correlation between gestational age at birth and creatine and GAA measures at CPA will also be determined using a Spearman or Pearson correlation. Preterm infant plasma and urine creatine and GAA concentrations and creatine:GAA ratio in the early postnatal period will be described and plotted. Associations between cerebral creatine content, plasma and urine creatine concentrations with maternal, and infant characteristics at CPA will be determined using Spearman or Pearson correlations for continuous data (maternal age, gestational age, birth weight, parity, gravity, placental weight) or a t-test or Mann-Whitney U test for categorical data (infant sex, mode of delivery, maternal comorbidities, country of birth, ethnicity, and dietary preferences), as appropriate. Differences in creatine, GAA, and amino acid content of nutrition sources (TNP, formula or breast milk) will be determined using a one-way ANOVA or Kruskal-Wallis H test as appropriate. The association between creatine, GAA, and amino acid content of nutrition sources (TNP, formula or breast milk) and infant plasma and urine creatine at CPA will be assessed using a Spearman or Pearson correlation as appropriate. Finally, the association between cerebral creatine content, plasma creatine levels, and the ratio of plasma:cerebral creatine at CPA with GMA, MRI global injury, and DAYC-2 scores will be determined using linear regression at both CPA and at 3 months’ corrected postnatal age. Potential confounders such as gestational age and maternal and infant characteristics will be assessed, along with collinearity, prior to performing multivariable linear regression.

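### The diet–creatine correlation at CPA takes no account of gestation at birth, and the unadjusted preterm–term test cannot show how much of its difference goes with current feed

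*Protocol article*

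**What the plan says.** Specific Aims sets out to "Compare cerebral, plasma, and urine creatine and GAA content between preterm and term infants at CPA". Statistical Analysis states the method: differences in creatine and GAA measures "between infants born preterm and those born at term will be assessed at CPA using a t-test or Mann-Whitney U test as appropriate". No covariate or stratum is attached. A correlation of gestational age at birth with the same measures is also planned, again without feed.

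For diet, the same section says that the association between nutrition content and "infant plasma and urine creatine at CPA will be assessed using a Spearman or Pearson correlation as appropriate". No term for gestational age or preterm/term status is attached. (The matching aim asks whether dietary source "is related to plasma or urine creatine concentrations in the early postnatal period", a different period from CPA. That mismatch is a separate matter.)

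The only adjustment in the section reads "Potential confounders such as gestational age and maternal and infant characteristics will be assessed, along with collinearity, prior to performing multivariable linear regression". It follows directly on the linear regressions of GMA, MRI and DAYC-2 scores.

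The data needed for adjustment will exist. Primary Outcome Measures includes creatine, GAA and "amino acid levels in infant nutrition (TPN, formula, or breast milk) supplied from birth until discharge and at CPA". Monitoring and Data Collection lists feeding in the 24 hours before each sample among the covariates and potential confounders. The sampling section takes a specimen of the current feed with the blood and urine. Infant feed is nevertheless absent from the characteristics that Statistical Analysis tests against creatine.

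**The concern.** Gestation at birth is fixed before any feed is given. It may influence what the infant is being fed at CPA, and under the study's own hypothesis it influences creatine. It is therefore a candidate confounder of the diet–creatine association. A simple correlation cannot separate the two: a deficit that belongs to prematurity can show up as a relation with diet, or can cancel a real one.

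The preterm–term test raises a milder question of interpretation. Its unadjusted result answers whether preterm infants have lower levels at CPA. It does not say how much of a difference accompanies the feed at sampling and how much lies beyond it. Readers will want that split, because the Introduction says the results may support creatine supplementation as standard nutritional care.

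**Working it through.** The article gives no figure on this point to reproduce. The check is structural, with simulations to show how size depends on unknown quantities.

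**Inputs from the article.** Recruitment and Sample Size: 20 infants per gestational group. Four preterm groups give 4 × 20 = 80, against 20 term, so the preterm fraction is π = 80/100 = 0.8. The tests are those named in Statistical Analysis.

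**Assumptions (not in the article).** Two-sided 5% level; feed shares; feed and preterm effects in SD units; term and preterm infants pooled in the diet correlation; the same feed effect in both groups.

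**Model.** y = b_feed·F + b_pre·P + e, with SD(e) = 1. P marks preterm birth. F marks the higher-creatine feed, used by a share qT of term and qP of preterm infants. Measured feed content is c = F plus noise of SD 0.3.

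**1. Diet correlation when diet has no effect (b_feed = 0).** 
cov(c, y) = b_pre · π(1−π) · (qP − qT). 
With b_pre = −1, qT = 0.8, qP = 0.4: cov = −1 × 0.16 × (−0.4) = 0.064. 
Mean share = 0.2 × 0.8 + 0.8 × 0.4 = 0.48, so var(c) = 0.48 × 0.52 + 0.09 = 0.3396. 
var(y) = 1 + 0.16 = 1.16. 
r = 0.064/√(0.3396 × 1.16) = 0.10, with no diet effect at all. 
If qP exceeds qT the sign reverses, and a real diet association can be masked.

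**2. Preterm–term difference when only feed matters (b_pre = 0).** 
Apparent difference = b_feed · (qP − qT). With b_feed = 1 and the same shares: 1 × (0.4 − 0.8) = −0.4 SD.

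**3. Simulated rejection rates**, 20 term and 80 preterm, 4000 runs per setting, effects of 1 SD:

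| Share on higher-creatine feed, term / preterm | Diet correlation: mean r, rejects | With preterm status in model | t-test: difference, rejects | With feed in model |
|---|---|---|---|---|
| 80% / 80% | 0.00, 5.0% | 4.9% | −0.01 SD, 5.4% | 4.8% |
| 80% / 60% | 0.05, 8.0% | 5.2% | −0.20 SD, 10.1% | 4.5% |
| 80% / 40% | 0.10, 17.2% | 5.6% | −0.40 SD, 29.7% | 5.6% |
| 80% / 20% | 0.16, 36.6% | 4.9% | −0.60 SD, 59.6% | 4.4% |

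With 15 term and 60 preterm infants, the three unequal rows give 6.8%, 13.9% and 28.6% for the correlation, and 10.2%, 23.7% and 47.0% for the t-test.

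**4. A second set of assumptions** (80 and 20 infants; formula shares preterm/term of 50%/30% or 60%/20%):
- Spearman correlation, no diet effect: 6.1% and 10.4% with a preterm deficit of 0.8 SD; 7.7% and 16.2% with 1.2 SD. Adjusted for preterm status: 5.0–5.2%.
- t-test, no preterm effect: 7.2% and 11.9% with a feed effect of 0.5 SD; 10.9% and 29.4% with 1.0 SD. Adjusted for feed: 4.8–5.6%.

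The t-test columns measure how often a purely feed-related difference would be detected. They count as errors only if the result is read as a difference beyond feed.

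**The case against.** **Feed is part of the hypothesis.** The Abstract and Discussion count a limited supply of creatine in newborn nutrition among the causes of depletion. A reader might infer that a preterm–term difference counts as depletion only if it persists at equal feed. The article does not support that rule: it would strip out a hypothesised cause and relabel nutritional depletion as no depletion. This objection stands, and it is why the unadjusted test should remain the main comparison.

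**Follow-on research.** A reader might also infer that a feed explanation and a synthesis explanation lead to different trials. The Discussion names only one, of dietary creatine supplementation, and either explanation could motivate it.

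**Size.** The Introduction says "a term infant most likely synthesizes between 64 and 93% of their daily creatine requirements", which leaves 100 − 93 = 7% to 100 − 64 = 36% from diet. It is tempting to turn this into a breast-milk-versus-formula contrast. The article does not say the range arises that way, describes both sources as low in creatine, and gives no link to plasma SDs. I do not rely on it. The feed shares, and any claim that feeding differs after intensive care, are likewise assumptions. At the mildest settings the inflation is negligible (6.1% and 7.2%).

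**Design.** Term infants are born at 39+0 to 40+6 weeks and the scan is at 40 weeks, so at CPA they are roughly newborn while preterm infants have been fed for weeks. A common feed effect is doubtful, and the adjusted estimate may extrapolate. This stands as a limit on the adjusted preterm estimate. The article also does not say that the diet correlation pools the groups. If it is preterm-only, gestation from 23+0 to 36+6 weeks can still confound it, but that case was not simulated.

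**Descriptive study, condensed article.** No significance level is stated and outcomes are called mainly descriptive, so rejection rates are only a yardstick. Covariate lists are often left to a fuller document. Here, however, the article names specific methods that, as stated, carry no covariates. Even if its confounder sentence were read more widely, it speaks of multivariable linear regression, which is not what is named for these two analyses.

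**Conclusion.** The point holds, most firmly for diet. The planned correlation cannot distinguish a diet association from a gestation effect, because gestation precedes feeding and may drive both variables. For the preterm–term test the point is narrower: the test is a valid total difference, but it is silent on how much of that difference goes with current feed, although the article itself lists feeding as a potential confounder.

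The size is unknown. It is zero when the feed mix is the same across gestation. Under the assumed scenarios false rejection is about 6% to 37% for the diet correlation and 7% to 60% for the t-test, if that is read as a difference beyond feed. Adjustment returns both to about 5%. All of these figures rest on feed shares and effects that the article does not give. The point concerns plasma and urine measures only and leaves the cerebral comparison untouched.

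**What to change.** For each CPA plasma and urine measure, add one linear regression on gestational age at birth (or preterm/term status) plus feed at CPA, entered as source and measured creatine content.

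- Take the diet association from this model instead of the raw correlation, and state which infants it includes.
- Keep the unadjusted preterm–term test as the main comparison. Report the feed-adjusted estimate beside it as supportive, described as the preterm difference beyond current feed.
- Do not make persistence at equal feed a condition for calling a difference depletion.

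This changes analysis wording only, since feed and gestation are already collected. The cost is the extra covariate information in a small sample. The adjusted estimate will be imprecise if feeds overlap little between groups or if feed is entangled with postnatal age; that should be reported where it occurs. Source and content may also carry much the same information, so the collinearity check already planned for the neurological regressions should be applied here too.
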